**Urinalysis:**

**Dipstick (A):**

Immediate site assessment for leukocyte\* and/or nitrite\*

**\*Urine culture:**

A mid-stream urine sample must be sent for culture upon a positive leukocyte and/or nitrite assessment based on dipstick at the site or upon Investigator suspicion of a UTI

**Routine urinalysis (B):**

- Glucose
- Ketone
- Specific Gravity
- Blood
- Urine pH
- Protein
- Nitrite
- Leukocyte/Leukocyte esterase

**Quantitative (C):**

- Albumin \*\*
- Creatinine \*\*
- Sodium, glucose, urea and creatinine (24-hour)\*\*\*
- cGMP
- Nitric oxide
- Prostanoids\*\*\*\*:  
Prostaglandins E2, D2 and I  
Thromboxane B2

\*\* at Visit 1 – albumin and creatinine will be measured

\*\*\* 24-hour measurements done only the day before Visits 3 and 12

\*\*\*\*if applicable, the appropriate and available assay to measure the prostanoid and/or its metabolite(s) will be performed

---

Albumin/creatinine ratio will be calculated.

An estimated glomerular filtration rate (eGFR) will be derived from serum creatinine values based on the MDRD formula:

**eGFR (ml/min)** =  $175 \times [\text{Serum creatinine (umol/L)} / 88.4]^{-1.154} \times [\text{age}]^{-0.203} \times [0.742 \text{ if subject is female}] \times [1.212 \text{ if subject is of African origin}]$

Subjects with normal renal function (defined as eGFR  $\geq 90$  ml/min) and mild impairment of renal function (eGFR  $\geq 60$  and  $< 90$  ml/min) will be eligible for the study. Subjects with

Proprietary confidential information.

© 2012 Boehringer Ingelheim International GmbH or one or more of its affiliated companies. All rights reserved.

This document may not - in full or in part - be passed on, reproduced, published or otherwise used without prior written permission.

moderate impairment (eGFR  $\geq 30$  and  $< 60$  ml/min) and severe impairment (eGFR  $\geq 15$  and  $< 30$  ml/min) will be excluded based on Visit 1 assessments.

The estimation of renal impairment as assessed at the screening visit will be used for inclusion (i.e. eGFR must be  $\geq 60$  ml/min). The exact baseline GFR will be assessed during Visit 3 under euglycaemia and will be the basis for the stratification of subjects in the hyperfilterer or non-hyperfilterer groups. As the results of the GFR will not be available until 3-4 weeks after the completion of the renal assessments during Visit 3, recruitment may continue until a minimum of 12 hyperfilterer subjects and 12 non-hyperfilterer subjects have completed the study (Visit 13). The rationale for this minimum is based on the sample size of 12 subjects per group, assuming that with a standard deviation of 5, a two-group t-test with a 0.05 two-sided significance level will provide an 80% power to detect a difference between the groups.

#### Criteria for hypoglycaemic events

Every episode of plasma glucose below or equal to 70 mg/dl (3.9 mmol/l) should be documented in the eCRF with the respective time and date of occurrence. Any hypoglycaemia with glucose values  $< 54$  mg/dl ( $< 3.0$  mmol/l) and all symptomatic and severe hypoglycaemias should be documented as an AE "hypoglycaemic event".

For the analysis, all hypoglycaemias will be classified according to the following criteria:

- Asymptomatic hypoglycaemia: Event not accompanied by typical symptoms of hypoglycaemia but with a measured plasma glucose concentration  $\leq 70$  mg/dl (3.9 mmol/l)
- Documented symptomatic hypoglycaemia with glucose concentration  $\geq 54$  mg/dl and  $\leq 70$  mg/dl ( $\geq 3.0$  mmol/l and  $\leq 3.9$  mmol/l): Event accompanied by typical symptoms of hypoglycaemia
- Documented symptomatic hypoglycaemia with glucose concentration  $< 54$  mg/dl ( $< 3.0$  mmol/l): Event accompanied by typical symptoms of hypoglycaemia but no need for external assistance
- Severe hypoglycaemic episode: Event requiring the assistance of another person to actively administer carbohydrate, glucagon or other resuscitative actions.

#### Follow-up on suspicion for urinary tract infections

Subjects having a history of chronic/recurrent urinary tract infections (UTI) or genital tract infection (GTI) will be identified and this condition must be documented under medical history / baseline condition in the eCRF. In case an acute episode of UTI or GTI is noted at screening, the subject will be screen failed and could later on be re-screened if the condition has been treated and resolved prior to re-screening.

For documentation of acute urinary tract infections during trial conduct, the following measures have to be taken:

Proprietary confidential information.

© 2012 Boehringer Ingelheim International GmbH or one or more of its affiliated companies. All rights reserved.

This document may not - in full or in part - be passed on, reproduced, published or otherwise used without prior written permission.

- In any case of suspected UTI (symptomatic or asymptomatic) a urine culture sample has to be taken and sent to the laboratory for confirmation of the diagnosis
- To be able to identify asymptomatic UTIs immediately, dipstick and urinalysis will be performed at the site at specified visits. Only in case of a positive dipstick for nitrite or leukocyte or in case of a suspicion of a UTI, a urine culture sample has to be taken and sent to the laboratory for confirmation of the diagnosis.

#### 5.2.4 Physical examination and electrocardiogram

At Visit 1 (baseline assessment done at screening), Visit 8 and Visit 13 (end of treatment), a complete physical examination will be performed by the investigator (see [Flow Chart](#)). Documentation of, and findings from the physical examination, must be part of the source documents available at the site.

Printed paper tracings from 12-lead ECGs (I, II, III, aVR, aVL, aVF, V1-V6) will be collected at Visit 1 (screening) and Visit 13 (end of treatment). In the event of any cardiac symptoms (i.e. suspicion of heart rhythm disorders or cardiac ischemia), additional ECGs will be recorded. All ECGs will be evaluated (signed, dated and commented upon) by the treating physician/investigator and stored locally. Any clinically relevant changes (according to investigators judgement) in the ECG will be reported as AEs and followed up and/or treated locally until a normal or stable condition if feasible is achieved.

All ECGs performed at any time during the conduct of the trial (whether clinically relevant or routine) will be stored in the subject source notes.

#### 5.2.5 Weight and waist circumference

Weight measurements should always be done on the same scale for each subject. In order to get comparable body weight values, it should be performed in the following way:

- after the urine sampling (weight after bladder voiding)
- shoes and coats/jackets should be taken off
- pockets should be emptied of heavy objects (i.e. keys, coins etc).

Waist circumference measurements should be made around a subject's bare midriff, after the subject exhales while standing without shoes and with both feet touching and arms hanging freely. The measuring tape should be made of a material that is not easily stretched, such as fibreglass. The tape should be placed perpendicular to the long axis of the body and horizontal to the floor and applied with sufficient tension to conform to the measurement surface.

Waist circumference should be determined by measuring the midpoint between the lowest rib and the iliac crest.

Proprietary confidential information.

© 2012 Boehringer Ingelheim International GmbH or one or more of its affiliated companies. All rights reserved.

This document may not - in full or in part - be passed on, reproduced, published or otherwise used without prior written permission.

## 5.3 OTHER

### 5.3.1 Other endpoint

#### 5.3.1.1 The Diabetes Treatment Satisfaction Questionnaire (DTSQ)

At Visit 3, Visit 8 and Visit 12, the Diabetes Treatment Satisfaction Questionnaire (DTSQ status version) will be used as a subject reported outcome. The DTSQ in its original status form (refer to [Appendix 10.1](#)) is recommended for measuring subject satisfaction with diabetes treatment. It consists of a six-item scale assessing treatment satisfaction and two items assessing perceived frequency of hyperglycaemia and hypoglycaemia. The DTSQ is recognized by the World Health Organization (WHO) and the International Diabetes Federation (IDF) as a useful instrument in assessing outcomes of diabetes care. The DTSQs will be analyzed descriptively only – statistical tests will not be conducted.

The DTSQs is suitable for administration as a paper questionnaire. In this trial, it will be self-administered by the subject. The scores will then be transcribed into the eCRF by the Investigator (or the designated site-personnel).

A subject can self-administer the DTSQs in approximately 5 - 10 minutes, and the Investigator (or designated site-personnel) should ensure that the subject has access to a quiet area at the site where they can be left alone to record a response to all the items displayed. *In instances where a subject cannot give or decide upon a response, no response should be recorded.* The Investigator (or designated site-personnel) should check that all items have been completed by the subject, but the response to each item should not be scrutinised.

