| Dispense BI 10773 25 mg O       |           |                |                                                            | X              |                |                |                | X        |                |                |                 |                |                |                                      |          |                |
| Medication compliance                      |           |                | X                                                          |                | X P | X P | X P | X        | X P | X P | X               | X              | X              | X                                    |          |                |
| Trial termination                          |           |                |                                                            |                |                |                |                |          |                |                |                 |                |                |                                      |          | X              |

Proprietary confidential information.

© 2012 Boehringer Ingelheim International GmbH or one or more of its affiliated companies. All rights reserved.

This document may not - in full or in part - be passed on, reproduced, published or otherwise used without prior written permission.

- A. Visits 2, 11 and if required EOT are the only clinic visits where a fasting status is required for labs. Visit 2 to be performed preferably within 1 week of Visit 1. If subjects discontinue the trial after the start of therapy and prior to completion of Visit 13, an end of treatment (EOT) visit should be done as soon as possible and the following will be performed: A physical exam including vitals, an ECG and laboratory assessments (FPG, HbA1c, ~~GA~~ ~~FA~~, Hematology, Chemistry, Lipids, Urine B and hCG). The EOT visit must be performed instead of a scheduled clinic visit for early discontinued subjects in cases where discontinuation occurs during a scheduled clinic visit. Early discontinued subjects should return to the clinic only for follow up Visit 15 (Visit 14 may be skipped). Refer to [Section 6.2.3](#) for details. If feasible, early discontinued subjects should continue with CGM and HBGM until Visit 15.

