##### Other exploratory diabetes mellitus endpoints:

The other exploratory diabetes endpoints include:

- Change from baseline in HbA1c after 8 weeks of treatment with BI 10773
- Change from baseline in ~~glycated albumin (GA)~~ **fructosamine (FA)** after 8 weeks of treatment with BI 10773
- Change in fasting plasma glucose from baseline
- Change in glycaemic exposure, variability and stability as derived from Continuous Glucose Monitoring (CGM) from baseline
- Change in parameters of glucose variability (as measured by CGM or home blood glucose monitoring [HBGM])
- Change in mean daily glucose (as derived from the 8-p HBGM)
- Change in AUC for glucose (CGM data) from baseline
- Change in basal, bolus and total insulin requirement from baseline
- Change in basal insulin requirement day vs night from baseline
- Change in the numbers of bolus boosts from baseline
- Change in UGE from baseline
- Change in BP from baseline
- Change in the Diabetes Treatment Satisfaction Questionnaire from baseline

Proprietary confidential information.

© 2012 Boehringer Ingelheim International GmbH or one or more of its affiliated companies. All rights reserved.

This document may not - in full or in part - be passed on, reproduced, published or otherwise used without prior written permission.

- Change in HbA1c, hypoglycaemia and insulin requirements from baseline (refer to [7.3.2](#) for details of responder classification)

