#### 6.2.2 Treatment period

Baseline renal assessments: Visits 3 and Visit 4 (prior to start of treatment on Day 3):

- Visit 3 and Visit 4 assessments will be performed as noted in the study Flow Chart and protocol. During Visit 3, subjects will undergo various renal and vascular assessments under controlled euglycaemia followed by the same assessments during Visit 4, where baseline renal and vascular measurements will be collected under controlled hyperglycaemia.
- The DTSQ should be completed by the subject at Visit 3.
- The trial medication (BI 10773) will be dispensed at the end of Visit 4.

Proprietary confidential information.

Treatment period: Day 3 to Visit 12 (Daily BI 10773 25 mg treatment):

- During clinic visits and phone visits, subjects will be reminded to continue the proper use of daily HBGM, log and diary maintenance and CGM (sensor change every 6 days and device calibration 2-3 times daily or as required using blood glucose values).
- Subjects will be given open-label 25 mg BI 10773 at the end of Visit 4 and will be instructed to start taking the study medication in the morning of study Day 3 and continue to take the study drug once daily in the morning (between 7-11 AM) except before clinic Visits 8, 11, 12 and 13 where they will be dosed at the clinic. During Visits 8, 11 and 12 a pre-dose PK sample is collected (prior to BI 10773 dosing). The timing of PK sample collection during Visit 11 and 12 should be **approximately** the same as during Visit 8.
- *For the next 5 days after Visit 4 (study Days 3-7), subjects must be followed up daily (phone calls) to ensure that all study safety and efficacy procedures are adequately followed. Details of daily follow up will be captured in eCRFs.*
- Subjects will be reminded at Visit 7 (phone call) about the requirement to perform an 8-point glucose profile using HBGM (study Day 28) the day before clinic Visit 8. The same will be done for the required 8-point glucose profile one day before Visit 11 (study Day 49).
- Subject will have physical exams done at Visits 1, 8 and 13 as described in the study Flow Chart and under Section 5.2.4.
- The DTSQ should be completed by the subject at Visit 8.
- During the telephone Visit 10, subjects should be reminded to come to the clinic in 1 week for clinic Visit 11 in a fasting state (no food or drinks, water only, for at least 10 hours).

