**6.2.3 End of trial and follow-up period**

Visits 14 and Visit 15

- Visit 14 and 15 assessments will be done at the clinic and procedures will be performed as noted in the study Flow Chart.
- Subjects will be reminded about the continued proper use of daily HBGM, log data entry and CGM (sensor change every 6 days and daily calibrations using HBGM values). Subject will return the CGM and equipments for HBGM at final clinic Visit (#15). Subjects will be reminded about the requirement to perform an 8-point glucose profile using HBGM one day after Visit 14 (study Day 66) and record the values in the study diary.
- For subjects who complete the study, with the exception of ~~GA FA~~ and HbA1c, only abnormal lab values per the investigator's judgement will be repeated at Visit 15 (under fasting conditions if needed). Subjects will be advised ahead of time if they are required to come to Visit 15 under fasting conditions

End of Treatment Visit (only required for early discontinued subjects)

- In case of premature discontinuation from the trial (after start of BI 10773 treatment and prior to completion of Visit 13), an end of treatment (EOT) visit should be done as soon as feasible. All early discontinued subjects must perform the following safety laboratory assessments under fasted conditions: FPG, HbA1c, ~~GA FA~~, Hematology, Chemistry, Lipids, Urine B, hCG
- Other assessments must also be performed as noted in the study Flow Chart for early discontinued subjects under the specific EOT visit including a physical exam, vitals and an ECG. The EOT visit must be performed instead of a scheduled clinic visit for early discontinued subjects in cases where discontinuation occurs during a scheduled clinic visit. These subjects should return to the clinic for an additional follow up visit (only Visit 15 required, Visit 14 may be skipped). If feasible, early discontinued subjects should continue with CGM and HBGM until Visit 15.

Proprietary confidential information.

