### 7.3 PLANNED ANALYSES

All individual values will be listed and standard statistical parameters (number of non-missing values, mean, standard deviation, median, quartiles and range) or frequency tables will be calculated separately for each treatment group (including the respective totals). The data recorded will be used to check whether the study protocol has been adhered to (e.g., inclusion and exclusion criteria, visit schedules etc.). Data from subjects that withdraw after the screening period and prior to Visit 3 will not be reported.

The statistical analysis will be based on the following populations:

- Treated Set (TS): The treated set (TS) will consist of all subjects who were treated with at least one dose of study drug.
- Full Analysis Set for Renal (FAS\_RENAL): The full analysis set (FAS\_RENAL) will consist of all subjects who were treated with study drug, have a baseline measurement and an evaluable post-dosing renal data under the clamped hyperglycaemia condition (Visit 13) for the primary endpoint.
- Full Analysis Set for Diabetes Mellitus (FAS\_T1DM): The full analysis set (FAS\_T1DM) will consist of all subjects who were treated with study drug, have a baseline measurement and an evaluable post-dosing diabetes mellitus data for the other endpoints.

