### **7.4 HANDLING OF MISSING DATA**

No special computations (e.g., interpolation, last value carried forward or similar) will be performed for the missing data.

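### The treatment satisfaction questionnaire is not given at the EOT visit, so some early stoppers have no post-dosing score and the Visit 12 summary covers only subjects still in the trial

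*Protocol*

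**What the plan says.** Section 5.3.1.1 schedules the questionnaire: "At Visit 3, Visit 8 and Visit 12, the Diabetes Treatment Satisfaction Questionnaire (DTSQ status version) will be used as a subject reported outcome". The DTSQs row of the Flow Chart agrees. It is marked at Visits 3, 8 and 12 and blank under EOT, Visit 14 and Visit 15. Section 6.2.2 repeats the mid-treatment administration: "The DTSQ should be completed by the subject at Visit 8".

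For early stoppers, Flow Chart footnote A describes the EOT visit as "A physical exam including vitals, an ECG and laboratory assessments", and the laboratory list that follows includes fasting glucose, HbA1c and fructosamine. Section 6.2.3 adds: "Other assessments must also be performed as noted in the study Flow Chart for early discontinued subjects under the specific EOT visit". Neither place mentions the DTSQs. Both say that when a subject discontinues at a scheduled clinic visit, the EOT visit takes that visit's place.

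Section 5.1.1 lists among the other exploratory diabetes endpoints: "Change in the Diabetes Treatment Satisfaction Questionnaire from baseline". Section 5.3.1.1 limits its analysis: "The DTSQs will be analyzed descriptively only – statistical tests will not be conducted". The analysis set for these endpoints, FAS_T1DM in Section 7.3, takes treated subjects who "have a baseline measurement and an evaluable post-dosing diabetes mellitus data for the other endpoints". Section 7.4 states: "No special computations (e.g., interpolation, last value carried forward or similar) will be performed for the missing data".

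**The concern.** A satisfaction score is most informative about a drug when it includes the people who gave the drug up. Here those people attend a visit at which other change-from-baseline diabetes endpoints are collected, but nobody asks them about satisfaction. At the last scheduled administration, Visit 12, the summary is then conditional on having stayed. In a single-arm trial there is no comparator in which the same selective loss could be seen.

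At stake is the reading of one exploratory, patient-reported endpoint. No hypothesis test and no sizing decision depends on it. The gap still differs from an ordinary analysis choice, because an analysis plan can decide how to summarise the scores but cannot recover a questionnaire that was never handed out.

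**Working it through.** **Figures available.** The protocol gives no expected DTSQ change, no DTSQ standard deviation and no dropout rate, so there is no stated figure to reproduce for this endpoint. The sample size in Section 7.6 concerns GFR and has no bearing here.

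**Step 1: what each early stopper contributes** (Flow Chart, footnote A, Sections 5.3.1.1 and 6.2.3).

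| Time of stopping | Visit 3 score | Visit 8 score | Score at stopping | Visit 12 score |
|---|---|---|---|---|
| Day 3 to before Visit 8 (Day 29) | yes | no | no | no |
| At Visit 8, EOT done in its place | yes | not scheduled | no | no |
| After Visit 8, before Visit 12 (Day 57) | yes | yes | no | no |
| At Visit 12, EOT done in its place | yes | yes | no | not scheduled |
| After Visit 12, before Visit 13 is complete | yes | yes | no | yes |

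From Day 3 until Visit 8 the scheduled contacts are telephone calls, so Visit 8 is the first on-treatment opportunity for the form. The first two rows may have no post-dosing score. The next two keep the Visit 8 score but are absent at Visit 12. Early stoppers return for Visit 15, where the form is not scheduled either.

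**Step 2: comparison with neighbouring endpoints.** In the EOT column of the Flow Chart, HbA1c, fructosamine, fasting glucose, weight, waist circumference and vital signs are all marked. The DTSQs is not, although Section 5.1.1 lists it alongside HbA1c, fructosamine and fasting glucose. No reason is given.

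**Step 3: size of a possible shift at Visit 12.** Let q be the share of subjects with no Visit 12 score, m_c the mean change in those with a score, and m_s the mean change that the others would have reported.

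- Mean over all subjects = (1 − q)·m_c + q·m_s
- Reported mean = m_c
- Shift = m_c − [(1 − q)·m_c + q·m_s] = q·(m_c − m_s)

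Assumptions, none from the protocol: the six satisfaction items, each scored 0 to 6 (Section 5.3.1.1, Appendix 10.1), are summed to 0–36; q is 2/30 or 6/30; and the gap m_c − m_s runs from −4 to +12 points. The 6/30 is an illustrative upper case, the difference between about 30 entered and the minimum of 24 completers in Section 7.6.

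| Gap (points) | q = 2/30 | q = 6/30 |
|---|---|---|
| −4 | −0.27 | −0.8 |
| 0 | 0 | 0 |
| +4 | +0.27 | +0.8 |
| +8 | +0.53 | +1.6 |
| +12 | +0.80 | +2.4 |

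For example, 6/30 × 8 = 1.6. A Visit 8 summary uses the same formula, but its q counts only those who stopped at or before Visit 8.

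**Step 4: what bears on the sign.** Section 3.3.4.1 lists adverse events, repeated hypoglycaemia and withdrawal of consent as grounds for leaving. Items 3, 7 and 8 of the questionnaire ask about low sugars, recommending the treatment and continuing it. That makes a positive gap plausible. The same section also lists interfering concomitant drugs, surgery, other diseases, pregnancy, eligibility violations and non-attendance, none of which need lower the score.

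**The case against.** The strongest defence is that Visit 8 is an on-treatment administration. A reader might infer that everyone who stops early disappears from the satisfaction result. The documents do not support that: a subject who stops after Visit 8 has a baseline and an on-drug score, and FAS_T1DM asks for post-dosing data, not completion. This stands, and it confines the complete loss to those who stop by Visit 8.

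A reader might also infer that the result is biased upward as a matter of fact. That is not shown either. With unrelated withdrawals the gap may be zero or negative, and so is the shift.

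Nor is 20% a planned dropout rate. Twelve per group is a minimum, and group membership is known only 3–4 weeks after Visit 3, so the surplus over 24 must also cover uneven groups.

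The DTSQ endpoint is defined only as a change from baseline, without a time point, so the choice of summary visit may properly sit in the analysis plan. That is right for the summary, but not for the collection of the data.

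Finally, a score at EOT is not necessarily an on-treatment score. The visit follows discontinuation, a new antidiabetic regimen may already have begun (Section 3.3.4.1), and the questionnaire asks about current treatment and the past few weeks. This stands, and it limits how EOT scores may be used.

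**Conclusion.** The point holds in a limited form. The DTSQs is missing from the EOT visit in every place that defines that visit, while comparable endpoints are collected there. Subjects who stop from Day 3 up to and including Visit 8 may have no post-dosing score, those who stop between Visits 8 and 12 have none at stopping, and the Visit 12 summary rests on subjects still in the trial.

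That summary may be biased, and upward is the more likely direction if stopping follows dissatisfaction or adverse events. Neither size nor sign can be fixed from the protocol. The range of −0.8 to +2.4 points at 6 of 30 missing rests wholly on the assumed sum score, share and gaps. Because the endpoint is exploratory, descriptive and untested in an open-label single-arm pilot, this is a worthwhile low-cost improvement. It does not threaten the trial's conclusions on GFR.

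**What to change.** 1. Add the DTSQs to the EOT column of the Flow Chart, to footnote A, and to Sections 5.3.1.1 and 6.2.3. Record with it the date of last dose and any change of treatment before the form was completed.
2. Report the number of subjects with a score at each visit.
3. Beside the observed Visit 12 result, show descriptively the last available post-baseline score (Visit 8, EOT or Visit 12), labelled by visit and time since last dose.

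The cost is matching edits in four places and a paper form that Section 5.3.1.1 puts at 5–10 minutes, at a visit that already takes place. The drawback is that EOT scores reflect different lengths of exposure and may be given after the drug was stopped. They should therefore supplement the Visit 12 summary, not replace it, and should not be called on-treatment scores.
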